### 5.15 Trades & Diversity Training Program (TDTP)

The TDTP is a federally-funded vocational construction skills training program. TDTP is funded through the Government of Canada’s Skilled Trades Awareness and Readiness Program initiative (15), which focuses on helping individuals who face barriers to employment to develop skills and experience they need to find a job or continue their education. The TDTP has been developed and will be delivered by Community Builders®, a social enterprise located in Minesing, Ontario, Canada (<https://www.communitybuilders.co/community-impact/training-and-employment/>). The TDTP is not part of a formal education program and does not lead to formal Red Seal certification for any of the construction trades. As part of the TDTP, Community Builders® provides a Case Manager for each cohort who regularly interacts with each apprentice to help them navigate external services and supports for any barriers that may exist or arise during training that threaten their ongoing participation or completion. TDTP is a cohort-based construction skills training program, with anticipated class sizes between 8 and 15 participants. Each cohort will experience structured activities over a 12-week period that include both in-classroom education and supervised hands-on experiential learning at participating construction sites. The in-class component will account for 22% (102 total hours) of the 12-week program. The in-class component will be led by the Construction Trainer, Case Manager, and Program Director. The in-class component will focus on teaching life skills needed for employment, referred to as the socio-economic & construction curriculum. The curriculum will include lessons about, but not be limited to the following: trade-specific vocabulary; trade math skills; ways to effective communication; conflict resolution in the workplace (referred to as soft skills); health and safety in the workplace; career / trade exploration; and interview and resumé-writing skills. The remaining 78% (360 total hours) will be spent on-site in supervised, hands-on learning. TDTP will target visible minorities, individuals who are Indigenous, and women for enrollment.

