Throughout the TDTP, the Case Manager teaches soft skills each Monday morning for three hours in-person in a classroom type setting. This teaching involves slide decks on a specific topic, hand-outs, discussion, and reflection questions. The Program Director teaches for 60 minutes on topics which include trade math skills, career exploration, and health & safety in the workplace. The Construction Trainer is involved in direct hands-on teaching with the apprentices on a variety of topics included in residential construction (drywall, painting, framing, flooring, etc.). Teaching on Mondays are at a ratio of one teacher to 8 to 15 apprentices. From Tuesdays to Thursdays, apprentices are out on job-sites with Community Builders’ mentors (ratio being 1:1). During these periods, apprentices are involved in hands-on work skills training with all aspects of residential construction, while being encouraged to use the learned soft skills (for example, conflict resolution). During the 12-week program, apprentices and all Community Builders’ staff use the *Slack* platform (<https://slack.com/>) to communicate with each other. This communication can be private (1:1 messages) or in a group channel.

Problems with apprentices are typically identified quickly by any of the of the Community Builders’ staff. While apprentices are encouraged to reach out to the Case Manager if they are feeling any distress, different types of issues are also identified through 1:1 conversations that may happen on the work sites with their mentors. If a construction mentor identifies that there is an issue that the apprentice is experiencing, they will reach out through *Slack* or directly contact the Case Manager. Once this occurs, the Case Manager initiates a conversation with the apprentice to explore the distressful issue(s). Where appropriate, the Case Manager will coach and assist the apprentice in setting goals and working through the issue(s). In circumstances that require external consultation to help resolve, the Case Manager will refer the apprentice to appropriate external resources (for example, the Canadian Mental Health Association).

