## 5.2 Rationale

In previous iterations of the TDTP, the Case Manager and Program Director have developed relationships with many other external agencies and service providers to facilitate access for their clients. Most of these relationships have involved basic communication and referrals, and would be described as minimally active relationships (16). For some problems, however, such as mental health and drug and alcohol addictions, the Case Manager has experienced difficulty in timely access to healthcare services. These delays have had negative consequences for program attendance and completion ([name], Program Director, personal communication). The Program Director has indicated that a more cooperative and coordinated relationship (16) with these services might benefit their clients. To this end, Community Builders® is partnering with Mental Health & Addictions (MH&A) services at the Royal Victoria Regional Health Centre (RVRHC) to develop a fit-for-purpose referral and access process that will ensure appropriate and timely care for those at-risk apprentices. As part of this novel case management strategy, we will also introduce a remote self-reporting tool for distress that will be completed by apprentices and monitored by the Case Manager to pre-emptively identify apprentices at-risk of absenteeism or drop-out with the hope that early identification and intervention will be more effective than the usual case management approach. A real-world (pragmatic) randomised study is therefore needed to compare the effectiveness of this Intensive Case Management approach compared to the usual Brokered Case Management approach for apprentices enrolled in the TDTP. This study is needed to demonstrate the superior benefits of ICM on important outcomes such as improved skills training retention and completion and post-training employment in order to justify its implementation across other vocational training programs with at-risk youth.

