
## 11.12 Web-based, self-report tool for distress

The Distress Thermometer screening tool will be integrated into a web-based, self-reporting tool that apprentices will be asked to complete on a daily basis (Monday to Thursday) prior to attending their in-class or on-site session for the 12-week duration of the TDTP. Apprentices whose cohorts are randomized to either ICM^10^ or ICM^11^ will be provided with a tablet computer to access the Distress Thermometer screening tool. Apprentices will login using a unique username and password system. The Case Manager will have immediate access to each apprentice’s daily distress score, including all of their previous scores. The scores will be prioritized according to the following criteria:

1. High Priority Distress score ≥ 4 + Answer “Yes” to last question, or

Answer “Yes” to last question

A referral may also be made if the apprentice’s distress level is escalating defined as a change of ≥ 2 on the distress score from previous day.

2. Medium Priority Distress score≥4 + Answer “No” to last question

3. Low Priority Distress score ≤3 + Answer “No” to last question

The Case Manager will immediately contact (by phone) all apprentices in the high priority group to coordinate a care management plan personalized for their identified stressor(s). For those apprentices identified as medium priority, a one-on-one in-person meeting with the Case Manager will be scheduled to occur within 48 business hours in order to coordinate a personalized care management plan for their identified stressor(s). For those apprentices identified as low priority, a quick check-in with the Case Manager will take place within the work week to determine if any special care management issues need to be addressed. The care management plan is not dictated by the study but is left to the discretion of the Case Manager and apprentice. The care management plan will be documented within the web-based, self-report tool.

For those apprentices who do not compete a daily assessment by 8 am, the Case Manager will reach out by email/phone immediately to the apprentice to enquire about their status. For those apprentices experiencing severe distress, they have the option of directly contacting (email/phone) the Case Manager instead of completing the Distress Thermometer screening tool.

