## 11.2 Mental health & addictions

When an apprentice has been identified as being in a high priority group due to a mental health or addictions stressor, the Case Manager will contact (by email or text message) the triage counsellor for the MH&A program intervention. After this initial contact, a standard referral form will be sent to the Case Manager at Community Builders to complete and return to the MH&A triage counsellor. The triage counsellor will review the referral form immediately and schedule an appointment with a MH&A healthcare provider. The timing of the appointment will be determined by the triage counsellor but will always occur within 24 to 48 hours of the referral. The triage counsellor will also determine the need for an in-person versus audio/video consultation.

For any apprentice identified as being at high risk for suicide, the triage counsellor will instruct the Case Manager to take the apprentice to the RVRHC Emergency Department where they will be assessed by the MH&A crisis team.

For any apprentice identified as being in either drug withdrawal or relapse, the triage counsellor will schedule an appointment with healthcare providers at the RVRHC Rapid Access Addiction Medical clinic. The appointment will always occur within 24 to 48 hours of the referral.

For any apprentice that requires treatment or admission to a MH&A program that limits their availability to complete the TDTP, they will be withdrawn from their cohort and enrolled in a subsequent TDTP cohort after resolution of their health-related issues. For all other apprentices who access MH&A services, they will continue to attend their TDTP and continue to be supported according to their allocated case management model.

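### Section 11.2 opens the MH&A pathway only to a high priority group that the self-report tool defines, so ICM01, which has the service without the tool, has no stated way in

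*Protocol*

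**What the plan says.** The MH&A pathway in Section 11.2 starts from one condition: "When an apprentice has been identified as being in a high priority group due to a mental health or addictions stressor". The Case Manager then contacts the triage counsellor, a referral form is completed, and an appointment follows within 24 to 48 hours of the referral.

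Priority groups come from Section 11.12. There, "The scores will be prioritized according to the following criteria", and the criteria use the daily distress score and the tool's closing yes/no question. A further trigger in the same section, a change of at least 2 points from the previous day, also needs tool scores. On who has the tool: "Apprentices whose cohorts are randomized to either ICM^10^ or ICM^11^ will be provided with a tablet computer to access the Distress Thermometer screening tool".

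Figure 1 in Section 5.3 places ICM01 in Barrie with the service and without the tool. Section 20.1 labels ICM01 as the MH&A programme arm, and Section 8 makes the service available at the Barrie site.

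Section 5.15 describes how problems are found without a tool: mentors, Slack messages and conversation. It continues: "In circumstances that require external consultation to help resolve, the Case Manager will refer the apprentice to appropriate external resources".

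**The concern.** In a factorial design each factor needs a delivery rule that works at both levels of the other. Here the rule for entering the service is written in terms of the other factor, the tool. Staff who follow Section 11.2 to the letter have a defined trigger in ICM11 and none in ICM01.

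If referral in ICM01 is left to individual practice, fewer apprentices may reach the triage counsellor than intended, or the threshold may differ between cohorts. Four analyses could be affected:

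- **ICM01 v BCM** would be diluted if ICM01 received less of the service than intended.
- **ICM11 v ICM01** would mix the effect of the tool with unequal formal entry to the service. Extra detection by the tool is a legitimate part of its effect. An entry rule written for only one of the two arms is not. This is the contrast most worth protecting, because the tool is what Section 8 randomises within site.
- **The tool-by-service interaction** in the three primary models (Sections 20.11a to 20.11c) draws on the same cells.
- **Time to access** (Section 12.21) runs from the Case Manager's referral to the appointment, so it depends on whether an ICM01 referral carries the 24 to 48 hour limit.

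**Working it through.** The plan states no figure on this point. The check is a comparison of the text by arm, followed by simple counts.

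**Step 1. Entry condition by arm** (Section 5.3 Figure 1, and Sections 8, 11.12, 11.2 and 20.1)

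| Arm | Site | Tool | MH&A service | Can be classed High Priority under 11.12 | Entry stated in 11.2 |
|---|---|---|---|---|---|
| BCM | Sudbury | no | no | no | not applicable |
| ICM10 | Sudbury | yes | no | yes | not applicable |
| ICM01 | Barrie | no | yes | no | none |
| ICM11 | Barrie | yes | yes | yes | yes |

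ICM01 is the only arm that has the service but cannot meet the written condition.

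**Step 2. Other possible routes into the service**

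- *Suicide risk, and withdrawal or relapse* (Section 11.2). These paragraphs drop the priority wording, for example: "For any apprentice identified as being in either drug withdrawal or relapse, the triage counsellor will schedule an appointment". Both describe what the triage counsellor does, and the second times the appointment from a referral. Neither says how the counsellor is reached other than by the contact in the opening paragraph.
- *Direct contact* (Section 11.12). Apprentices in severe distress are told that "they have the option of directly contacting (email/phone) the Case Manager instead of completing the Distress Thermometer screening tool". This is an alternative to completing the tool, so it is addressed to tool users.
- *Usual case management* (Section 5.15). This needs no tool, but it leads to external resources in general. It is not linked to the triage contact or the appointment limit.

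None of these gives a referral criterion for ICM01.

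**Step 3. How much of the trial ICM01 represents**

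- Apprentices: Section 14.1 gives 400, split equally by site. 400 / 2 = 200 in Barrie. With 1:1 allocation of the tool (Section 8), 200 / 2 = 100 in ICM01, and 100 / 400 = 25%.
- Cohorts: Section 14.1 gives 20 to 34 per site. Half without the tool is 10 to 17.
- Contrasts: ICM10, ICM01 and ICM11 are each compared with BCM (Section 20.1), and ICM11 is compared with ICM10 and with ICM01 (Sections 6.2 and 7.1). That is 3 + 2 = 5 contrasts. With 3 primary outcomes, 5 × 3 = 15.
- Contrasts that involve ICM01: ICM01 v BCM and ICM11 v ICM01, so 2 × 3 = 6 of 15.

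The counts show where ICM01 appears, not how large any distortion is. The protocol gives no referral rate and no share of ICM01 referrals expected to reach the triage counsellor, so dilution cannot be calculated.

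**The case against.** The strongest reply is that the intention is plain and staff will act on it.

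- Section 5.2 presents the service as a partnership to "develop a fit-for-purpose referral and access process that will ensure appropriate and timely care for those at-risk apprentices", a better referral route for the Case Manager and not an extension of the tool.
- Section 8 makes availability depend on site.
- Section 7.2 compares time to access in ICM01 with BCM, which presupposes referrals without the tool.
- Section 12.21 counts from the Case Manager's referral and mentions no priority class.
- Section 11.2 closes by saying that apprentices who use the service stay under their allocated case management model, which in Barrie means ICM01 or ICM11.
- The opening of Section 11.2 does not cite Section 11.12 and could be read as Case Manager judgement.

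Most of this stands. A reader might infer that ICM01 gets no service at all and that the factorial design collapses. The documents do not support that: the passages above show that use without the tool is expected, and the bar on ICM01 exists only on the literal wording. What the reply does not supply is the criterion. The only definition of high priority is the tool's, and nothing attaches the triage contact or the appointment limit to a referral made by usual means.

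A reader might also infer a matching gap in ICM11, because an apprentice who contacts the Case Manager instead of screening has no answers that day. This is weak. The option takes the apprentice straight to the person who makes referrals, and nothing suggests that the service would be withheld for want of a score.

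Two further limits hold. ICM01 v BCM is also Barrie v Sudbury, and clearer wording does not change that. The protocol also offers no way to separate extra detection by the tool from unequal formal entry.

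**Conclusion.** The point holds as a defect in a stated delivery rule: Section 11.2 makes entry to the service depend on a classification that one of the two service arms cannot receive. Entry in ICM01 could therefore be lower than intended or inconsistent between cohorts. About 100 of 400 apprentices are concerned, in 10 to 17 cohorts, with 6 of 15 pairwise primary-outcome contrasts, the interaction term in three primary models, and time to access. The direction for ICM01 v BCM would be dilution if entry is lower. The size is unknown.

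This rests on reading high priority in Section 11.2 as the class defined in Section 11.12, on equal allocation of the tool within Barrie, and on counting ICM11 v BCM under Section 20.1. It is worth correcting before cohorts are enrolled, since an analysis plan cannot repair uneven delivery afterwards. It does not show that the arm fails.

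**What to change.** Amend Section 11.2 to say that:

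1. In both Barrie arms the Case Manager may refer to the MH&A triage counsellor any apprentice in whom a mental health or addictions problem needing external help is identified by the usual routes in Section 5.15 (mentor report, Slack, conversation).
2. The 24 to 48 hour appointment limit applies to every such referral.
3. In ICM11, a High Priority screen with a mental health or addictions stressor is an additional trigger.

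The investigators should set the exact threshold, the same in both Barrie arms. Section 5.15 offers possible wording in describing the Case Manager's role, "any barriers that may exist or arise during training that threaten their ongoing participation or completion", but that describes a general role. Making it a mandatory referral rule would be a clinical and workload decision.

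Report referrals by arm where consent and data collection allow. The qualification matters because Sections 15 and 16.3 describe consent only for cohorts given the tool, and the action and date fields in Section 18.11 sit under the tool's data. Whether they will be filled for ICM01 is not settled.

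The cost is a few sentences, covered in the site training already planned in Section 23.3. Sample size and randomisation do not change. The downside is possibly a few more referrals to the MH&A service.

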## 11.3 Compliance

To promote study enrollment and adherence with study-related tasks, each enrolled apprentice will be provided with a tablet computer for the duration of the TDTP to support their participation and promote adherence to daily screening with the Distress Thermometer self-reporting tool. Apprentices who complete ≥ 90% of their daily Distress Thermometer screens will receive $50 for their time and effort and be enrolled in a draw for 5 tablet computers. The Apprentices enrolled in ICM^10^ and ICM^11^ do have the option of not completing the Distress Thermometer screening tool. These apprentices will be asked to relate the reason for each episode of non-compliance from a fixed list available in the self-report tool. Apprentices who choose not to complete the Distress Thermometer screening tool but document the reason will be considered to be compliant for that episode.

# 12 Outcomes

## 12.1 Primary outcome measures

### 12.11 Program attendance

Difference in proportion of absence-free program days (AFDs) at 12 weeks from the start date of the TDTP, where ***absence-free days are defined by the cumulative number of days of program attendance during the 12-week study period.*** The potential number of AFDs for each apprentice is the cumulative number of program days that the apprentice is alive during the 12-week TDTP, with a maximum of 48 days (=12 weeks x 4 days/week). A day is defined as an 8–10-hour work-day during the TDTP from Monday to Thursday. An apprentice is considered to have attended a work-day as long as the Case Manager or their construction supervisor documents their attendance.

### 12.12 Program completion

Difference in proportion of drop-outs at 12 weeks from start date of TDTP, where ***a drop-out is defined as an apprentice who fulfils any of the following criteria:***

- Has missed more than 50% of training days, or
- Who has elected to leave the program for reasons other than taking another job or returning to school

The proportion of drop-outs is defined as the ratio between the cumulative number of apprentices who meet the criteria for drop-out relative to the cumulative number of apprentices enrolled in the TDTP.

### 12.13 Post-program employment

Difference in proportion of full-time employment at 24-months post-TDTP completion, where ***full-time employment is defined as paid work ≥ 30 (median) hours per week at their main or only job.*** The reference period that will be used to determine full-time employment is the 4-week period preceding the 24-month post-TDTP completion date. The criteria for full-time employment will be considered to be met if the hours worked are reported as <30 hours per week for the following reasons: vacation; maternity; seasonal business; labour dispute; weather. Full-time employment will be self-reported by the TDTP graduate, and consent for corroboration with the employer will be requested by the study team. The proportion of full-time employment is defined as the ratio between the cumulative number of TDTP graduates who fulfill full-time employment criteria relative to the total number of TDTP graduates. A TDTP graduate is defined as any apprentice who successfully completed the TDTP (Section 12.12).

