# 5 Background and Rationale

## 5.1 Background

### 5.11 Youth unemployment

In 2019, 67.3% of young Canadians aged 15 to 30 were employed (1), a rate that was approximately 15% lower than older individuals. Employment rates are lowest among those aged 15 to 19 (60.2%), compared to rates exceeding 80% in those older than 20. Part of these differences are due to lower participation rates among young Canadians aged 15 to 19 due to school attendance. However for those not in school, these Canadians were also more likely to be unemployed (over 15%) compared to those aged 20 and older (<10%). Among young Canadians, there were minor differences in employment rates between men/women and Canadian-born/immigrants. In contrast, education levels had a profound impact on differences in employment rates. For those without a high school diploma, only 52.2% were employed compared to high school graduates (75%) or post-secondary education (>88%). Even after accounting for education, employment rates among Indigenous youth are 20% lower than their non-Indigenous counterparts. Of those employed, 44.3% of those aged 15 to 19 are employed in full-time permanent jobs, meaning they work ≥30 hours per week and have no pre-determined end date, while another 53.2% work in either part-time or non-permanent jobs, a rate that is 2-fold higher than those aged over 20. The rate of involuntary part-time or non-permanent employment has also displayed a disturbing trend with a rate that is almost 10% higher today compared to 30 years ago, reflecting increased difficulty in finding full-time employment. Some young Canadians are neither in employment, education nor training (NEET), and they are at high risk of chronic unemployment, social disengagement and poor quality of life. The prevalence of NEET among young Canadians is as high as 12.2% in men and 14.8% in women, with little differences due to education or immigrant status. Among Indigenous youth, approximately 3 out of 10 never finish high school, and unemployment rates can be as high as 70% on reserves (2). Visible minorities, persons other than Indigenous peoples who are non-Caucasian in race or non-white in colour, are also disadvantaged in employment opportunities (2,3). For example, even among university-educated visible minorities, the unemployment rate is 50% greater than non-racialized groups. Identifying these young Canadians and providing them with career skills training and opportunities is crucial for their full participation in society.

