## 14.3 Difference in proportions of full-time employment

Differences in full-time employment proportions between the groups is expected to be similar to differences in proportions of TDTP program completion.

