### 18.13 Study-specific data

| Data | Description | Data type |
| --- | --- | --- |
| **Cluster criteria** |  |  |
| City | Barrie vs Sudbury | Categorical |
| Enrollment | Quarter-year  Quarter (Q):  Q1=January 1 – March 31  Q2=April 1 – June 30  Q3=July 1 – September 30  Q4=October 1 – December 31 | Categorical |
| **Primary Outcomes** |  |  |
| Program completion | Yes | Categorical |
|  | No |  |
| Employment (full-time at 24 months) |  | Categorical |
| Self-report | Yes | Categorical |
|  | Employer verified |  |
|  | Employer not verified |  |
|  | No |  |
| **Secondary Outcomes** |  |  |
| Date/Time |  | Continuous |
| Mental health consult | ddmmyy:hh |  |
| Addictions consult |  |  |
| TDTP Satisfaction Survey | National Centre for Vocational Education Research Student Outcomes Survey (21) | Categorical |
| Distress Thermometer |  |  |
| Acceptability survey | Section 12.25 | Categorical |
| Feasibility survey | Section 12.26 | Categorical |

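### The full-time employment exception requires neither a job held in the 4-week window nor usual hours of at least 30, so a graduate on seasonal or weather layoff can be scored as full-time

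*Protocol*

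**What the plan says.** Section 12.13 defines full-time employment as "paid work ≥ 30 (median) hours per week at their main or only job". The reference period "is the 4-week period preceding the 24-month post-TDTP completion date". An exception follows: the criterion also counts as met "if the hours worked are reported as <30 hours per week for the following reasons: vacation; maternity; seasonal business; labour dispute; weather". The section sets no minimum number of hours under the exception and no condition on usual hours. It does not say that a job must be held during the window. No other section adds such a condition.

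On the source of the data, the same section states: "Full-time employment will be self-reported by the TDTP graduate, and consent for corroboration with the employer will be requested". The denominator is program graduates. Section 18.13 lists the variable "Employment (full-time at 24 months") as yes (employer verified or not verified) or no. It lists no field for actual hours, usual hours or the reason for short hours.

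Section 14.3 gives no separate power calculation for this outcome. It says only that the difference in full-time employment "is expected to be similar to differences in proportions of TDTP program completion", which leads back to the 0.10 difference and the power table of Section 14.2.

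**The concern.** The exception has a sound purpose: a person with a full-time job should not be scored a failure because a fixed window fell during a holiday, a strike or bad weather. That purpose needs a full-time job from which the person is temporarily away, and the text does not ask for one. Two kinds of graduate can therefore be scored as successes on the wording as it stands:

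- one laid off for the season or by weather, with no hours in the window;
- one in a seasonal job that never reaches 30 hours, who gives the seasonal nature of the business as the reason.

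The program trains people for construction, where season and weather are ordinary reasons for short hours, so the exception may be used often. The third primary objective (Section 7.1) is to reduce unemployment, and the rule can record a person without work as a success. Follow-up is exactly 24 months after completion, so each cohort's window falls at the same time of year as its program ended. Use of the exception may therefore vary with the calendar timing of cohorts.

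**Working it through.** **1. What the wording admits.**

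| Graduate in the 4-week window | Base definition | Exception as written |
|---|---|---|
| Usual hours 30 or more, short for a listed reason | not met | met (intended) |
| Laid off for season or weather, zero hours | not met | met on a literal reading |
| Seasonal job always under 30 hours, season given as reason | not met | met on a literal reading |
| Regular part-time job, no listed reason | not met | not met |

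If the median in the base definition is taken over the four weekly values, it is the mean of the middle two. One short week among three weeks of 30 hours or more then leaves the median at 30 or above. On that reading the exception is needed only when at least two of the four weeks are short, so it works mainly on longer interruptions.

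**2. The plan's own power figures.** Inputs from Section 14.2: two-sided alpha 0.05, difference 0.10, control proportion 0.75 or 0.80, and 20 × 10, 33 × 6 or 25 × 8 participants per group. The intracluster correlation is 0, except 0.05 in scenario 2. With n per group divided by the design effect 1 + (M − 1) × ICC, and p̄ the mean of the two proportions:

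power = Φ( [d − 1.96 √(2p̄(1 − p̄)/n)] / √([p₁(1 − p₁) + p₂(1 − p₂)]/n) )

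This gives 70.7, 54.7, 70.3, 70.7, 80.2, 79.8 and 80.2%, against the stated 70.6, 54.6, 70.2, 70.6, 80.2, 79.8 and 80.2%. All seven reproduce within 0.1 point.

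**3. Equal misclassification.** Let q be the share of graduates who are not truly full-time but are counted as full-time. The observed proportion is p + q(1 − p). With the same q in both groups, the observed difference is d(1 − q). The protocol gives no value for q, so those below are assumptions. Power is at 200 per group with ICC 0.

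| q | Difference | Power, control 0.75 | Power, control 0.80 |
|---|---|---|---|
| 0 | 0.10 | 70.7% | 80.2% |
| 0.1 | 0.09 | 65.0% | 75.2% |
| 0.2 | 0.08 | 58.8% | 69.3% |
| 0.3 | 0.07 | 52.3% | 62.8% |

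Check for q = 0.2, control 0.75: 0.75 + 0.2 × 0.25 = 0.80 and 0.85 + 0.2 × 0.15 = 0.88, a difference of 0.08. The ratio of the proportions not full-time stays at 0.12/0.20 = 0.60, the same as 0.15/0.25, so only the risk difference shrinks.

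These proportions are completion rates carried over through Section 14.3. The protocol states no 24-month employment rate.

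**4. Unequal misclassification.** With 0.75 versus 0.85 and shares q_c (control) and q_t (intervention), the observed difference is 0.10 + 0.15 q_t − 0.25 q_c.

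- q_c = 0.1, q_t = 0.3: 0.10 + 0.045 − 0.025 = 0.12.
- q_c = 0.3, q_t = 0.1: 0.10 + 0.015 − 0.075 = 0.04.

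The difference is inflated whenever q_t exceeds 0.25/0.15 = 1.67 times q_c. Equal shares cannot be taken for granted. The mental health and addictions service exists only in Barrie (Section 8), so its contrast is Barrie versus Sudbury, where seasonal work may differ. Reporting is also unmasked self-report (Section 17).

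**The case against.** The strongest reply is that the exception should be read with the definition it qualifies. The definition speaks of paid work at a main or only job, and the exception requires the listed reason to explain the short hours. On that reading a graduate without a job has no hours to excuse, and a standing part-time job does not qualify. This is a fair account of what was probably meant, and part of it stands: an ordinary part-timer without a listed reason is excluded. A reader might infer that part-time workers in general become successes, and the text does not support that. But the intended reading is nowhere written down, and a zero-hours seasonal layoff fits the wording.

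A second reply is that Section 18.13 lists variables and is not the 24-month questionnaire, which may ask for hours. That is possible and cannot be seen from the protocol. Even so, the listed data hold only the final yes or no, and employer verification helps only if the employer is asked about usual hours.

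A third reply is that the employment model in Section 20.11c includes year-quarter and its interaction with each intervention. These terms address variation between periods. They do not correct a wrong classification of individuals.

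Three further inferences are tempting and should be resisted:

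- That the treatment difference must shrink. This holds only for the risk difference, and only with equal shares.
- That cohorts ending in winter are scored mostly through the exception. The protocol has no figure for this.
- That the background contradicts the rule, because Section 5.11 describes full-time permanent jobs as "meaning they work ≥30 hours per week and have no pre-determined end date". That sentence explains a national statistic on permanent jobs. Permanence is not part of the trial outcome.

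**Conclusion.** The point holds as a defect in the wording of a primary outcome. As written, the exception can score a graduate with no hours, or with a job that is always short, as full-time employed. The listed data would not allow the error to be found or reversed.

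The size cannot be determined from the protocol. Under equal reclassification, the risk difference falls by the factor 1 − q, from 0.10 to between 0.09 and 0.07 for an assumed q of 0.1 to 0.3. Under unequal reclassification it can move either way, to 0.04 or 0.12 in the examples shown. The best power in Section 14.2 is 80.2%, so there is little room for dilution if Section 14.3 is taken at its word. The power losses rest on completion rates standing in for employment rates, on 200 per group and on zero intracluster correlation. They are illustrative, not predictions.

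**What to change.** Reword Section 12.13 so that the exception applies only when the graduate holds a job during the 4-week reference period and the usual hours at that job, when not affected by the listed reason, are at least 30 per week. State that a graduate with no job in the window, or with usual hours below 30, is not full-time.

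Add usual weekly hours, actual weekly hours and the reason for any shortfall to the 24-month contact, to the employer corroboration request and to the list in Section 18.13. Report a sensitivity analysis in which the exception is not applied.

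The cost is a short change to Section 12.13, a few extra items at a contact already planned, and one further run of the same model. The observed full-time proportion will probably be somewhat lower in every arm. The legitimate purpose of the exception is kept.
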